## Abstract

**Background:**

Fear of cancer recurrence, depressive symptoms, and cancer-related fatigue are prevalent symptoms among cancer survivors, adversely affecting patients’ quality of life and daily functioning. Effect sizes of interventions targeting these symptoms are mostly small to medium. Personalizing treatment is assumed to improve efficacy. However, thus far the empirical support for this approach is lacking. The aim of this study is to investigate if systematically personalized cognitive behavioral therapy is more efficacious than standard cognitive behavioral therapy in cancer survivors with moderate to severe fear of cancer recurrence, depressive symptoms, and/or cancer-related fatigue.

**Methods:**

The study is designed as a non-blinded, multicenter randomized controlled trial with two treatment arms (ratio 1:1): (a) systematically personalized cognitive behavioral therapy and (b) standard cognitive behavioral therapy. In the standard treatment arm, patients receive an evidence-based diagnosis-specific treatment protocol for fear of cancer recurrence, depressive symptoms, or cancer-related fatigue. In the second arm, treatment is personalized on four dimensions: (a) the allocation of treatment modules based on ecological momentary assessments, (b) treatment delivery, (c) patients’ needs regarding the symptom for which they want to receive treatment, and (d) treatment duration. In total, 190 cancer survivors who experience one or more of the targeted symptoms and ended their medical treatment with curative intent at least 6 months to a maximum of 5 years ago will be included. Primary outcome is limitations in daily functioning. Secondary outcomes are level of fear of cancer recurrence, depressive symptoms, fatigue severity, quality of life, goal attainment, therapist time, and drop-out rates. Participants are assessed at baseline (T0), and after 6 months (T1) and 12 months (T2).

**Discussion:**

To our knowledge, this is the first randomized controlled trial comparing the efficacy of personalized cognitive behavioral therapy to standard cognitive behavioral therapy in cancer survivors. The study has several innovative characteristics, among which is the personalization of interventions on several dimensions. If proven effective, the results of this study provide a first step in developing an evidence-based framework for personalizing therapies in a systematic and replicable way.

**Trial registration:**

The Dutch Trial Register (NTR) NL7481 (NTR7723). Registered on 24 January 2019.

## Background

Depressive symptoms, fear of cancer recurrence, and cancer-related fatigue are prevalent symptoms among cancer survivors. It is estimated that 22–87% of cancer survivors report moderate to severe fear of cancer recurrence and 8–21% of cancer survivors meet criteria of depression, based on diagnostic interviews or exceeding a cut-off of clinically significant symptoms on self-report measurements [1, 2]. Severe fatigue is also highly prevalent during and after cancer treatment, in at least a quarter of cancer survivors [3, 4]. Presence of fatigue, depression, and/or fear of cancer recurrence is associated with impaired quality of life and daily functioning. In addition, depressive symptoms, fear of cancer recurrence, and fatigue often co-occur and can exacerbate each other [1–3, 5, 6].

Previous studies evaluated interventions for fear of cancer recurrence, depression, and fatigue in cancer survivors or patients with cancer [7–12]. The vast majority of these interventions are based on a cognitive behavioral model which assumes that although cancer and cancer treatment may trigger the psychological symptoms and fatigue, cognitive and behavioral factors subsequently perpetuate the symptoms [7, 8, 11]. Interventions targeting these perpetuating factors have been shown to decrease symptoms and improve functioning. However, effect sizes are mostly small and sometimes of a moderate magnitude, especially for the treatments aimed at fear of cancer recurrence and depressive symptoms [7, 10, 12]. Also, treatment effects are not always sustained at long-term follow-up [8] and attrition rates are relatively high [13].

Tailoring interventions to specific patient characteristics and needs is assumed to improve treatment effectiveness and increase treatment engagement and adherence [14]. Therefore, there has been a repeated call for the personalization of psychological interventions for cancer patients [15–17]. Despite its intuitive appeal, there is, however, insufficient evidence to support this assumption. A few studies have applied personalization in cognitive behavioral therapy (CBT) for cancer survivors or patients with cancer [18–28]. However, to the best of our knowledge, only one of these studies made a head-to-head comparison between the efficacy of personalized CBT to standard CBT [19]. Results from this study, in which a CBT program was tailored by using diagnostic profiles in patients with cancer-related pain, showed greater improvement in patients receiving personalized CBT immediately after treatment, 1 month after treatment and at 6 months follow-up. To determine if personalized CBT has added value over standard CBT, more studies are needed in which a head-to-head comparison is made. Therefore, in this study, we compare the efficacy of personalized CBT to standard CBT in cancer survivors with moderate to severe fear of cancer recurrence, depressive symptoms and/or cancer-related fatigue.

CBT can be personalized in several ways and on various dimensions. In this study, CBT is personalized on multiple dimensions in order to create maximal contrast between personalized and standard CBT: (1) the allocation of treatment modules based on ecological momentary assessments, (2) treatment delivery (face-to-face, internet-based or blended), (3) patients’ needs regarding the symptom for which they want to receive treatment, and (4) treatment duration. Below, these dimensions are described in more detail.

### Allocation of treatment modules

In most intervention studies so far, all patients receive the same treatment protocol, consisting of a fixed set of treatment modules. One of the research directions in the field of personalizing CBT has focused on allocating treatment modules to individual patients [29]. For example, in an intervention for cancer-related fatigue in cancer survivors, the presence of potential maintaining factors is identified with corresponding questionnaires. If a maintaining factor appears to be present, the associated treatment module is added to the treatment plan [30, 31]. Although personalized to some extent, the norm scores used to determine if a treatment module should be allocated are still based on nomothetic (i.e., group-based) research data. Further, the presence of a specific maintaining factor does not automatically imply a causal relationship between the maintaining factor (e.g., a disturbed sleep-wake rhythm) and the symptom of interest (e.g. cancer-related fatigue). Innovative technologies such as ecological momentary assessments (EMA) can establish temporal associations between (maintaining) factors and symptoms of interest [32]. EMA delivers personalized and contextualized information. Therefore, EMA is suited for systematically personalizing interventions and adjusting treatment on an individual level. As the specific maintaining factors in a specific individual can be identified and targeted, the associated treatment modules can be more confidently assigned to the patient.

### Treatment format

The format in which the treatment is delivered can also be personalized. Currently, most research studies include only one treatment form: patients receive either face-to-face, Internet-based, or a mix of these, called blended treatment. In order to provide care adjusted to individual patient’s needs, patients should be able to choose one of these three formats [33].

### Patients’ needs

Allowing patients to choose their most burdensome symptom for which they want to receive psychological treatment seems relevant in personalizing treatment. As previously mentioned, psychological symptoms often co-occur and previous research showed that the presence of clinically relevant levels of a psychological symptom does not automatically imply a need for psychological care for this symptom [34–37]. For example, depressive symptoms can be severe, but not causing hindrance or disability. Personalization could mean that psychological treatment focuses on treating the most burdensome symptom, for which the patient would like to receive psychological care. A previous meta-analysis indicated that following patients’ treatment preferences was associated with lower dropout rates [38].

### Treatment duration

Previous studies showed that there are large individual differences in how quickly patients respond to psychological interventions [39, 40]. Therefore, a standard treatment duration is not always appropriate. Patients could be actively involved in the decision when to end treatment. For example, treatment may be ended when patients feel to have improved sufficiently or to a “good enough level” [39]. This level could be determined by both the patient and the therapist, for example by evaluating to what extent goals have been reached or by evaluating the progress that has been made. Treatment duration and/or focus of treatment could be adjusted accordingly.

### Aims of the current study

The aim of this study is to investigate if personalized CBT is more efficacious than standard CBT in cancer survivors with moderate to severe fear of cancer recurrence, depressive symptoms, and/or cancer-related fatigue. Primary outcome is limitations in daily functioning. Secondary outcomes are symptoms of fear of cancer recurrence, depression, and cancer-related fatigue; quality of life; goal attainment; drop-out rates; and therapist time needed for treatment delivery. We hypothesize that personalized CBT, in this study defined as an intervention tailored to characteristics and needs of the individual patient, will lead to fewer limitations in daily functioning than standard CBT. We also expect that personalized CBT will lead to less symptoms of fear of cancer recurrence, depression, and cancer-related fatigue; better quality of life; higher goal attainment scores; and lower drop-out rates than standard CBT. Finally, we hypothesize that personalized CBT will not increase the time spent by therapists to deliver the intervention.

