### Study design

This randomized controlled trial is designed as a non-blinded, parallel group, two-arm superiority trial with a 1:1 allocation ratio. The two treatment arms are (a) personalized cognitive behavioral therapy and (b) standard cognitive behavioral therapy. Patients in the standard treatment arm receive an evidence-based protocolized CBT for depressive symptoms, fear of cancer recurrence, or cancer-related fatigue. Patients in the personalized treatment arm also receive CBT for depressive symptoms, fear of cancer recurrence, or cancer-related fatigue. However, the treatment in the personalized treatment arm is systematically tailored to the individual. Tailoring takes place on four dimensions: (1) the allocation of treatment modules, (2) treatment delivery (face-to-face, internet-based or blended), (3) patients’ needs regarding the symptom for which they want to receive treatment, and (4) treatment duration. Primary outcome (limitations in daily functioning) and secondary outcomes (symptom level and quality of life) are evaluated at baseline (T0) and 6 months (T1) and 12 months (T2) after intake. At the end of treatment, goal attainment is evaluated and therapist time is assessed. Drop-out rates are measured during the study. The overall study design is illustrated in Fig. 1. The study protocol has been approved by the Medical Ethics Committee of Amsterdam UMC, University of Amsterdam, Amsterdam, the Netherlands (reference no. 2018_277). The study is registered in the Dutch Trial Registry (NTR): NL7481 (NTR7723).

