*Goal attainment* is measured with the Goal Attainment Scaling (GAS) procedure. GAS is a method of scoring the extent to which patient’s individual goals for the treatment are achieved. Patients will a priori (at the start of psychological treatment) establish individual criteria for a successful outcome. Each goal is rated on a 5-point scale, with the degree of attainment captured for each goal area. Then, goals are weighted according to their difficulty, and eventually, after end of treatment, goal attainment is evaluated. For details, see Turner-Stokes [58]. This assessment method is included as it concerns a personalized outcome measurement, in which treatment is evaluated based on outcomes specifically relevant and important to the individual patient. Goal attainment is measured at the end of treatment. At this time point, the mean score is compared between both groups.

Therapists register their *time spent on each patient during treatment*. This includes preparation time, registration time in the patient data files (summarizing session), the number of sessions, and time needed to formulate e-consults or feedback in Internet-based or blended therapy. Therapist time is assessed after end of treatment. At this time point, the average time is compared between both groups.

*Drop-out rates* are collected for both treatment arms. In this study, a drop-out is defined as patients who discontinue the intervention before the planned end of the intervention. Patients’ reasons for discontinuing the intervention or declining to fill out follow-up questionnaires will be collected. Drop-out rates at T1 and T2 are compared between both groups.

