### Statistical analyses

#### Primary and secondary study parameter(s)

Descriptive statistics will be used to describe baseline characteristics of the experimental and control group and a chi-square test or independent *t*-test will be used to compare baseline characteristics of dropouts and completers in the total sample. Intention to treat analyses will be conducted, i.e., all randomized patients are included and are analyzed in their randomly assigned treatment group. For the intention to treat analyses, linear mixed-model analyses will be performed to evaluate changes in patient functioning from baseline to 6 and 12 months of follow-up (T1 and T2) and differences therein between the experimental group and the control group. Condition, time, and a group × time interaction will be added to the model (as fixed effects) to test for differences between the groups in treatment effects over time. In addition, a random intercept will be used to allow individuals to differ in the level of their outcome variables. Treatment center and manner of referral (self-referral versus referral by treating doctor) will be used as covariates. Based on pooled pre-test standard deviations, effect sizes will be calculated for the estimated differences between T0, T1, and T2 between groups. A significance level of *p*<0.05 is used in all analyses. Since linear mixed model analysis can handle missing observations due to dropout (assuming data are missing at random), imputation of missing values will not be needed. However, patterns of missing data will be explored and predictors of missing data analyzed, especially if these vary by treatment arm. If the primary analysis shows significant effects of personalized CBT, additional sensitivity analyses will be conducted using different assumptions about the value of missing values. Statistical analyses will be performed using SPSS 24.0. The statistical procedure as described above will also be followed for secondary study parameters (fatigue, depressive symptoms, fear of cancer recurrence and quality of life) without the sensitivity analyses. The independent *t*-test will be used to analyze differences between both groups with respect to goal attainment and therapist time.

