Previous studies showed that there are large individual differences in how quickly patients respond to interventions [39, 40]. In this study, we aimed to adjust treatment duration on the individual level by adding an “in-between” assessment and evaluating the extent to which treatment goals already have been reached after completing several treatment modules. If treatment continues, the second EMA determines which treatment modules to add or repeat. A previous study in which personalized CBT was compared to standard CBT in a non-cancer population found a beneficial effect of personalized CBT and suggested that this beneficial effect was found because the therapeutic sessions were longer [85]. The current study will provide additional information on the needed treatment duration in personalized CBT compared to standard CBT, and on the extent to which treatment duration differs within the personalized CBT group. Although we will not conduct cost effectiveness analyses, we will have an indication of the costs by therapist time and number of treatment sessions.

In conclusion, this study meets the repeated call for personalized psychological treatment, and the movement towards patient-centered care. This study is an important step, as it will provide much needed evidence regarding if personalized CBT is more efficacious than standard CBT. One could argue that therapists already aim to deliver personalized treatments in clinical practice. However, the challenge is to develop an evidence-based framework for personalizing CBT in a systematic and replicable way [86]. The explicitly operationalized personalization dimensions in this study have the potential to provide the first step in developing this kind of framework.

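### The plan hypothesises no increase in therapist time but names only a t-test for a difference, and a non-significant result from that test cannot support the hypothesis

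*Protocol article*

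**What the plan says.** Under Aims of the current study, the Protocol article lists directional hypotheses of benefit (functioning, symptoms, quality of life, goal attainment, drop-out) and closes with a claim of a different kind: "Finally, we hypothesize that personalized CBT will not increase the time spent by therapists to deliver the intervention".

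Under Secondary outcomes, the planned comparison of therapist time is: "At this time point, the average time is compared between both groups". Under Primary and secondary study parameter(s), the test is named: "The independent *t*-test will be used to analyze differences between both groups with respect to goal attainment and therapist time". The same paragraph sets the level: "A significance level of *p*<0.05 is used in all analyses".

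Study design gives superiority as the only framework: "This randomized controlled trial is designed as a non-blinded, parallel group, two-arm superiority trial with a 1:1 allocation ratio". The article states no largest acceptable increase, confidence-limit criterion or power for therapist time. The sample size calculation covers the primary outcome only.

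The Discussion says what the result is for. No cost-effectiveness analysis is planned, but "we will have an indication of the costs by therapist time and number of treatment sessions".

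**The concern.** The other hypotheses claim a difference, and a test for a difference suits them. The therapist-time hypothesis claims that time is no greater, and rejecting equality does not establish that unless time falls significantly. In every other case the only result compatible with the hypothesis is p>0.05, and that result becomes more likely as the data become noisier or fewer.

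The direction of the effect is open by design. In the standard arm, Table 2 puts the end of treatment at about 6 months after intake. In the personalized arm, treatment can run up to 8 months and patients may choose a fully face-to-face format. They may also finish early or choose internet-only delivery.

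The result will be used. It serves as the cost indication, and the Discussion cites a trial in a non-cancer population whose benefit was put down to longer sessions. If the primary outcome favours personalized CBT, readers will ask whether it took more therapist time.

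**Working it through.** **Inputs from the Protocol article.** Two-sided level 0.05. 152 evaluable patients, that is 76 per arm. 190 enrolled, that is 95 per arm. The dropout step reproduces: 152 / (1 − 0.20) = 190. There is no power figure for therapist time to reproduce, and nothing below depends on how the 152 was obtained.

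**Assumptions.** The article gives no mean or SD for therapist time, so effects are in SD units. Patients are treated as independent. The range of 76 to 95 per arm is used because the 20% allowance was set for the primary outcome; therapists register their own time, so data loss may be smaller.

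**Step 1: chance that the t-test misses a true increase.** With n per arm and a true increase of d SD, the t statistic has 2n − 2 degrees of freedom and noncentrality d × √(n/2). The miss probability is 1 minus the power for detecting an increase.

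| True increase | 76 per arm | 95 per arm |
|---|---|---|
| 0.1 SD | 91% | 90% |
| 0.2 SD | 77% | 72% |
| 0.3 SD | 55% | 46% |
| 0.4 SD | 31% | 22% |
| 0.5 SD | 14% | 7% |

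A miss is more likely than not only for increases below 0.32 SD (76 per arm) or 0.29 SD (95 per arm).

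**Step 2: what a non-significant result leaves open.** The 95% half-width is t(0.975; 2n − 2) × √(2/n).

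- 76 per arm: 1.976 × 0.1622 = 0.321 SD
- 95 per arm: 1.973 × 0.1451 = 0.286 SD

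An observed increase just short of significance equals the half-width, so its upper limit is twice that: 0.64 SD (76 per arm) or 0.57 SD (95 per arm).

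**Step 3: what a margin-based analysis could deliver.** With a true difference of zero and the upper limit of a two-sided 95% interval compared with a margin M, power is Φ(M / √(2/n) − 1.96).

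| Margin | 76 per arm | 95 per arm |
|---|---|---|
| 0.2 SD | 23% | 28% |
| 0.3 SD | 46% | 54% |
| 0.4 SD | 69% | 79% |
| 0.5 SD | 87% | 93% |

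The smallest margin with 80% power is (1.960 + 0.842) × √(2/n), which is 0.45 SD (76 per arm) or 0.41 SD (95 per arm). A margin of 0.3 SD would need 175 per arm.

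**Step 4: scale.** If the SD were 30% to 50% of the mean (an assumption without a source in the article), 0.3 SD would be 9% to 15% more time per patient. Margins of 0.41 to 0.45 SD would be about 12% to 23%.

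**The case against.** A reader might infer that the investigators plan to count p>0.05 as support. The article does not say so. It says that averages are compared and differences analysed. A significant decrease would be valid support and a significant increase valid contradiction. This stands: the fault is a decision rule that leaves the commonest ambiguous result unaddressed, not a planned wrong conclusion.

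A reader might also infer that any real increase would probably be missed. Step 1 does not support that: 0.5 SD would be detected with 87% to 93% power.

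Nor can it be said without qualification that the planned size supports the right analysis. Step 3 shows that it does so only for wide margins, and each therapist works in one arm, so correlation within therapists would lower precision further.

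Therapist time includes preparation, record-keeping and e-consults. It is therefore not a clean measure of therapy dose, and a margin test on it would not settle the session-length question.

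Finally, an article condenses a full protocol, and a margin for a secondary outcome could lie in a document not shown. A missing margin alone would be no finding. But the article states both the hypothesis and the test, and the two do not match.

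**Conclusion.** The point holds in limited form. The named test cannot confirm the stated hypothesis unless therapist time falls significantly, and the plan does not exclude reading a non-significant result as support. With 76 to 95 independent patients per arm, that result would occur in 77% to 72% of trials if the true increase were 0.2 SD and in 55% to 46% if it were 0.3 SD. It could coexist with an increase of up to about 0.57 to 0.64 SD. Without an SD in the article, these figures cannot be turned into minutes. Clustering within therapists is not included and would make the picture worse. This is one secondary outcome; neither the primary conclusion nor the sample size is affected. The correction is worth making because it is cheap and the result is meant to inform costs.

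**What to change.** Under Primary and secondary study parameter(s), separate therapist time from goal attainment and report the mean difference (personalized minus standard) with its two-sided 95% confidence interval. Then choose one of two routes.

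- **(a) With a margin.** The sponsor fixes the largest acceptable increase before unblinding. If the upper limit lies below it, conclude only that personalized CBT does not increase therapist time by more than the margin. Report an increase whenever the lower limit exceeds zero, even if the upper limit is below the margin. Both can occur when the margin exceeds the full interval width, about 0.57 SD at 95 per arm or 0.64 SD at 76. Call any result that meets neither criterion inconclusive.
- **(b) Without a margin.** If none can be justified, restate the hypothesis as estimation of the difference with its interval.

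Under both routes, state that p>0.05 is not evidence of no increase.

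The cost is one paragraph and, for (a), agreement on one number. No new data or patients are needed. The downside is that the claim becomes harder to make: 80% power is available only for margins of about 0.41 to 0.45 SD or wider, and less if time is correlated within therapists.
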